**2. Socio-psychological factors [Perception of impossibility to screening]**

In a survey in general population based in Ethiopia regarding routine screening while the majority of respondents reported that routine screening was beneficial [2, 64]. Given the high social status of health professionals, the shortage of healthcare services (mammography) and the arguably universal psychological tendency to obey authority, women may be unlikely to oppose the recommendation of physicians and healthcare institutions [2, 65].

**3. Socio demographic characteristics and knowledge of breast cancer and its screening**

A community based study in 2005 in USA on intervention to increase screening mammography among women 65 and older shows adjusted correlates of breast screening included higher education, perceived access to screening services, fear of result, and fear of discrimination positively correlated toward breast screening [66].

A Cross sectional study conducted in 2011 on assessment of Knowledge of Breast Cancer and Screening Methods among nurses university hospitals in north Ethiopia showed that knowledge on breast cancer, ever heard of breast screening and its services, attending formal education, high awareness about the benefits of screening, low stigmatized attitude were strongly associated with uptake of breast screening [59]. In the same study and other breast self-examination studies, unemployment and self-perceived high risk of breast cancer were associated with initial willingness. However, only being unemployed and house wife was associated with not to be screened [59, 67, 68].

With reference to the review, literatures showed research on breast screening uptake should move from the problem definition stage to the next phase of assessing the value of interventions among women. And also it has a clear indication of further research is required to develop new simple, brief, and effective interventions to boost breast screening uptake. Thus, taking these and other questions in to account which has to be answered, this study will conducted on the effect of community based health promotion intervention on breast cancer screening uptake among reproductive age women of Ethiopia using modified health belief model.

**BC ill health perception Modifying factors Likelihood of BC screening uptake**

**- Perceived benefits from breast screening**

**- Perceived barrier to breast screening**

**- Sociodemographic characteristics**

**- Socio-economic characteristics**

**- Socio-psychological characteristics**

**- Knowledge about breast cancer and breast cancer screening**

**Health motivation**

Perceived susceptibility to breast cancer

Perceived severity of breast cancer

Likelihood of performing behavior

(Uptake of screening)

**Perceived threat of Breast cancer**

**Cues to breast cancer screening**

Self-efficacy to undergo breast screening and use related services

**- Past behavior related to breast cancer and breast screening**

**- Distal factors**

# Fig 1: Conceptual framework of the research

# CHAPTER THREE: MATERIALS AND METHODS

## 3.1. Study Area and Period

This study will be conducted in reproductive age women of Hadiya Zone in southern Ethiopia. Hadiya zone is among the thirteen zone southern nations, nationalities and peoples of Ethiopia. The zone has ten woredas and two city administrations and 332 kebeles and “kifleketemas”. Its capital city is Hossana which located 230 km South East of capital city Addis Ababa and 194 km form the regional city Hawassa. The estimated population of the Zone is 1,650,104. The male population is 817,626, and the estimate of females in child bearing age (15-49) is 193,967. In the zone, in each kebele, there is at least one health center and health post. The total number of health institution by type is corresponding to kebele numbers and more. The communicable and some non-communicable diseases prevention work is being done by health extension workers and community health agents. Study period will be conducted from March to November 2018.

## 3.2. Study Design

A cluster randomized controlled trial proceeded by cross sectional study lasting for six months will be used to evaluate effectiveness of the community based educational intervention among women of reproductive age groups in Hadiya zone in southern Ethiopia. In fact, in first phase, qualitative method is employed for designing and developing the intervention.

## 3.3. Population

**For quantitative part,**

**3.3.1.** The source population will be women of reproductive age (15-49) who are living in

Hadiya Zone during the study period.

**3.3.2.** The study population will be women of reproductive age (15-49) who will be sampled

from the source population and fulfilled inclusion criteria.

**For qualitative part**, in phase 1, focus group discussions and in-depth interviews will be conducted with women and health workers (health extension workers, medical directors, and disease prevention and health promotion officers).

## 3.4. Inclusion and Exclusion Criteria

### 3.4.1 Inclusion criteria:

1. Women in reproductive age group
2. Women who are physically, mentally capable to provide informed consent, and can follow intervention provided without any support
3. Willing to participate and give data to the researcher.

### Exclusion criteria:

1. Participant who has already attended another intervention program.
2. Participants who cannot stay until the intervention is completed/moveable participants during intervention time

## 3.5. Sample Size and Sampling Technique

### 3.5.1. Sample size determination

For cluster level intervention, the sample size is calculated using double population proportion formula for cluster randomized trial [76, 77], with the assumption of the percentage of screening rate (π_0_) at the base line is similar in both groups; and Z_α/2_ the standard normal variable, at α = 5%; Z_β_ is (1-β) = 80%; **π_0_** is the prevalence of the participants who have knowledge about breast self-examination as screening methods since the affordable behavior is BSE (77.6%) [78]; a variable which gives maximum sample size; **π_1_** is the prevalence of screening rate in the intervention cluster/ kebele (87.6%) (Assumed to be increased by 10%); k is coefficient of variation of true proportions of the outcome variable between the clusters within each group. Since there is no study to estimate k, it is taken as 0.25.

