**Modifying factors**

**Past behavior related to breast screening and experience of screening**

A randomized controlled study conducted in USA on routine breast screening in migrant women shows; more than half agreed to breast screening, with no new symptoms detected [49]. Common reasons for not screening were perceived low risk and self-reported breast screening previously and being younger age, Hispanic ethnicity and having another screening during the visit were independently associated with breast screening [61].

A study conducted in the United States on evaluation of acceptability of breast cancer screening shows acceptance was generally higher among women at high risk for acquiring than among low-risk persons [49, 61]^.^

A cross sectional study conducted on behavioral survey for breast screening in Addis Ababa among the general population those who didn’t have adequate knowledge of breast cancer, considered themselves at low risk [62]. In another cross sectional study, the findings revealed that only 156 (57.8%) of them were knowledgeable about breast cancer and its screening and 114 (42.2%) were not [59].

According to Ethiopian cancer (oncology) report in 2016, about 33.4% out of the total is breast cancer which accounts 6% of all deaths in Ethiopia [59, 63]. The perception they have in positive or negative way leads women to consider oneself to be at medium or high chance of infection were looking breast mass, breast inflammation, experience from others, being female and unrecognized pain in breast, lack of awareness and feeling of health and economic issue and negligence [63].

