**(1.96+0.80)^2^ X [0.79(1-0.776) + 0.876(1-0.876)]**

**n = _________________________________________**

**[0.876-0.776]^2^**

**n**= **245** for each groups

Because, our study is cluster randomized trial, we assumed design effect 1.5 by cluster sampling method to overcome the design effect. Then, the sample size will be:

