**245*1.5 = 367.5 ≈ 368**

Finally, sample size further increased by 10% to account for contingencies such as non-response or recording error, i.e. 368 X 10/100 + 368= 404.8 ≈ **405**. Therefore, the final sample size will be 405 women for each group. Hence, the total number of study clusters/kebeles will be 30 i.e.15 kebeles in each arm based on WHO cluster sampling recommendation and then proportionally distributed according the number population in the cluster [69].

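### Section 3.5.1 says the 77.6% control rate gives the maximum sample size; under the formula shown it does not, and no candidate variables are listed to support a narrower meaning.

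*Protocol*

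**What the plan says.** The protocol, section 3.5.1 (Sample size determination), sets a two-sided 5% level and 80% power. The control rate π0 is 77.6%, the prevalence of knowledge of breast self-examination in a cited source, and it is described as "a variable which gives maximum sample size". The intervention rate π1 is 87.6%, so the assumed effect is 10 percentage points. The only formula displayed is the unpooled comparison of two proportions.

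The section reports 245 per group. For clustering it says "we assumed design effect 1.5 by cluster sampling method to overcome the design effect", which gives 368. It then says "sample size further increased by 10% to account for contingencies such as non-response or recording error", which gives 405 per group and 810 in total, in 15 kebeles per arm. It also sets a coefficient of variation between clusters, k, at 0.25, but k appears in none of the displayed arithmetic. No other variable, rate or resulting sample size is listed.

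Chapter Two, under past behaviour and experience of screening, cites a cross-sectional study in which "only 156 (57.8%) of them were knowledgeable about breast cancer and its screening".

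**The concern.** A maximum-sample-size argument tells the reader that the planning rate was chosen on the safe side. For two proportions a fixed distance apart, the binomial variance is largest when the rates lie either side of 50%. A pair as high as 77.6% and 87.6% is well away from that point and needs comparatively few women.

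This matters because the control rate is uncertain. The main outcome in the participant flow chart is screening uptake, whereas the 77.6% is a knowledge prevalence. If uptake in the control kebeles is mid-range, 405 per arm do not give the stated 80% power for a 10-point rise. A null result could then be read as coming from an adequately powered trial.

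**Working it through.** **Inputs (all from section 3.5.1 unless noted).** Two-sided α = 0.05, z = 1.96. Power 80%, z = 0.8416. π0 = 0.776, π1 = 0.876. Design effect 1.5. Allowance for loss ×1.1. 405 women in 15 kebeles per arm, so 405/15 = 27 per kebele on average. k = 0.25. Counterexample rate 57.8% (Chapter Two).

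**Reproducing the plan's figure.** The displayed formula is n = (z sum)² × [π0(1−π0) + π1(1−π1)] / (π0−π1)².

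- With the numbers as printed (0.80 in place of 0.8416, and 0.79 once in place of 0.776): 2.76² × [0.79×0.224 + 0.876×0.124] / 0.01 = 217.5, not 245.
- With 0.776 and the correct z sum: 2.8016² × 0.2824 / 0.01 = 221.7.
- A continuity-corrected two-proportion formula gives 245 exactly. Then 245×1.5 = 367.5, rounded to 368, and 368×1.1 = 404.8, rounded to 405, as stated.

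The gap between 218 and 245 is a separate matter. The ranking of rates below is the same with either formula.

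**Where the maximum lies.** With π1 = π0 + 0.10, the bracket is S = 0.495 − 2(π0 − 0.45)². It peaks at π0 = 45% (45% v 55%) with S = 0.495. At 77.6% it is 0.495 − 2×0.326² = 0.2824, which is 57% of the peak. Because S is symmetric about 45%, every control rate between 12.4% and 77.6% needs more women than 77.6% does. This ratio does not depend on the z values.

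| π0 | S | n per arm, displayed formula, correct z | n per arm, continuity-corrected | Power at effective n 245 | Power at effective n 270 |
|---|---|---|---|---|---|
| 77.6% | 0.2824 | 222 | 245 | 84% | 87% |
| 57.8% | 0.4622 | 363 | 386 | 63% | 68% |
| 45% | 0.4950 | 389 | 412 | 60% | 65% |

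The effective n is 405/1.1/1.5 ≈ 245 once the 10% allowance is used up, or 405/1.5 = 270 with no loss. Power is Φ(0.10/√(S/n) − 1.96). At 57.8% and n = 245, for example, √(0.4622/245) = 0.0434, 0.10/0.0434 = 2.302, and Φ(0.342) = 0.63.

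**Rates at which 405 per arm reach 80%, given the 1.5.** Setting n = 245 gives S = 245×0.01/7.849 = 0.3121. Then (π0 − 0.45)² = (0.495 − 0.3121)/2 = 0.0914, so π0 = 0.45 ± 0.302, which is 14.8% or 75.2%. Power is at least 80% at or beyond those limits and below 80% between them.

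**What k = 0.25 would imply.** The protocol shows no formula that uses k, so this step applies the standard coefficient-of-variation approach with k equal in both arms.

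- Intracluster correlation at 77.6%: k²π0/(1−π0) = 0.0625×0.776/0.224 = 0.217. Design effect: 1 + 26×0.217 = 6.6.
- Variance of the difference: [0.2824/27 + 0.0625×(0.776² + 0.876²)]/15 = [0.01046 + 0.08560]/15 = 0.00640. Standard error 0.0800. Power Φ(0.10/0.0800 − 1.96) = Φ(−0.71) ≈ 24%.
- Conversely, a design effect of 1.5 with 27 per kebele means an intracluster correlation of 0.5/26 = 0.019, hence k = √(0.019×0.224/0.776) ≈ 0.07.

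The stated k and the design effect used are therefore far apart.

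**The case against.** The strongest reply is that the phrase refers to a variable, attached to one citation. It may mean only that, of the variables considered, this one gave the largest number. On that reading the algebra over all rates does not make the phrase false. This is fair, and it limits the point: the protocol lists no candidates, so the statement cannot be checked and stands unsupported.

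A reader might infer that the plan offers 405 per arm as safe for every possible control rate. The protocol does not say that; it makes the maximum claim about its choice of variable and goes no further.

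The 57.8% is also limited evidence. It is a composite of knowledge about breast cancer and its screening, from a different study, and nothing shows that it was ever a candidate. A reader might infer that it should replace 77.6% and that about 600 women per arm are needed (363×1.5×1.1 ≈ 599). The documents do not support that. It shows only that a rate cited in the protocol gives a larger number.

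A third objection concerns k. In the coefficient-of-variation approach with k = 0.25 and 27 per kebele, the ordering reverses: about 76 clusters per arm at 77.6%, 53 at 57.8% and 40 at 45%. This is correct, but it does not rescue the phrase, because k is absent from the displayed calculation. It does mean that the point must stay tied to the formula shown, and that no unconditional power figure should be written in.

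Finally, a power shortfall is not established. The protocol gives no uptake rate for these women, and its review calls self-examination among female teachers in one zone very low. At 5% to 10%, the displayed formula needs only about 137 to 196 per arm before inflation.

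**Conclusion.** The concern holds in a limited form. Under the only formula shown, with a fixed 10-point rise, 77.6% does not give the maximum sample size: it needs about 222 per arm before inflation, against 363 at 57.8% and 389 at the peak of 45%. On the narrower candidate-variable reading, the statement is unsupported.

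The power figures of about 84%, 63% and 60% rest on a design effect of 1.5, a normal approximation, and an effective 245 per arm after the 10% allowance. With no loss they rise to 87%, 68% and 65%. They do not use k = 0.25. With that value, power at 77.6% would be about 24%, so none of these figures is secure until k and the 1.5 agree.

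The finding does not show that the trial is underpowered at its true, unknown control rate, nor that more women must be enrolled. It shows that a stated property of the planning rate is wrong or unsupported, and that 405 per arm should not be taken as a worst case.

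**What to change.** In section 3.5.1:

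1. Delete the statement that the chosen variable gives the maximum sample size, and do not present 405 per arm as a worst case. If a comparison of candidate variables was made, list the candidates with their rates and resulting numbers.
2. State power conditionally: only if the design effect is 1.5, 405 per arm (effective number about 245 after 10% loss) give about 84% power for a 10-point rise at a control rate of 77.6%, 63% at 57.8% and 60% at 45%. Add that 80% is reached only at control rates of about 75% or more, or about 15% or less.
3. State that these figures do not use k = 0.25, which with 15 clusters of 27 per arm would imply a design effect of about 6.6 and power of about 24% at 77.6%. Reconcile k with the 1.5 before any power is quoted.

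The cost is a change of wording and a less favourable power statement. This correction needs no extra enrolment.

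### Section 3.5.1 states two incompatible, unsupported clustering assumptions (k = 0.25 and a design effect of 1.5); the 80% power holds only under the second

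*Protocol*

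**What the plan says.** All inputs are in Protocol section 3.5.1. It targets 80% power at a 5% level for an increase from 77.6% to 87.6%. It defines a between-cluster quantity, "k is coefficient of variation of true proportions of the outcome variable between the clusters within each group", and gives it a value: "Since there is no study to estimate k, it is taken as 0.25". The displayed formula is the ordinary one for two independent proportions and has no k term. It is said to give 245 women per arm. The text then states "we assumed design effect 1.5 by cluster sampling method to overcome the design effect", which takes 245 to 368, and a 10% allowance takes 368 to 405. The number of clusters has a separate origin: "the total number of study clusters/kebeles will be 30 i.e.15 kebeles in each arm based on WHO cluster sampling recommendation". The protocol does not mention k again.

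**The concern.** k and the design effect describe the same thing, namely how much the true proportion varies between kebeles. Once the proportion and the cluster size are fixed, either one determines the other, so a plan cannot choose both freely. Here one is stated and dropped, and the other is applied without derivation. If they disagree, the stated 80% depends on which one is believed.

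The main comparison, screening behaviour in intervention against control kebeles, rests on this figure. If the true variation is near the stated k, a null result would say little about the intervention. Enrolling more women in the same kebeles would not help, because the number of kebeles is then the limit.

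**Working it through.** **Inputs (Protocol 3.5.1).** p0 = 0.776, p1 = 0.876, difference d = 0.10, two-sided 5% level, 15 kebeles per arm. Women per kebele: m = 368/15 = 24.5 before the 10% allowance, 405/15 = 27 after it. Write V = p0(1−p0) + p1(1−p1) = 0.2824 and S = p0² + p1² = 1.3696.

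**The plan's own figure.** The printed formula does not return 245. It gives 217.5 as typed (with 0.79 and z = 0.80), 215.2 with 0.776 in place of 0.79, and 221.7 with z = 0.84 as well. The pooled formula gives 225, and with a continuity correction 245. From there 245 × 1.5 = 367.5 (368) and 368 × 1.10 = 404.8 (405). So the chain can be reproduced, and k appears nowhere in it.

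**What a design effect of 1.5 implies.** From 1 + (m−1) × ICC = 1.5:
- ICC = 0.5/26 = 0.019 at m = 27, and 0.5/23.5 = 0.021 at m = 24.5.
- k = √[ICC(1−p)/p], which is 0.075 to 0.078 at 77.6% and 0.052 to 0.055 at 87.6%.
- As one common k, √[0.5V/(mS)] = 0.062 to 0.065.

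**What k = 0.25 implies.** From ICC = k²p/(1−p):
- At 77.6%, ICC = 0.0625 × 0.776/0.224 = 0.217, a design effect of 6.1 (m = 24.5) to 6.6 (m = 27).
- At 87.6%, ICC = 0.0625 × 0.876/0.124 = 0.44.

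At the control rate the two assumptions differ about threefold in k and tenfold in ICC.

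**Power with 15 kebeles per arm.** The examples use m = 27 and the normal approximation. The ranges add m = 24.5 and a t reference on 28 df.
- Design effect 1.5: SE = √(0.2824 × 1.5/405) = 0.0323; power = Φ(0.1/0.0323 − 1.96) = 0.87. Range 81 to 87%.
- k = 0.25 in both arms: SE = √[(0.2824/27 + 0.0625 × 1.3696)/15] = √(0.0961/15) = 0.080; power = Φ(0.1/0.080 − 1.96) = 0.24. Range 22 to 24%.
- Common ICC of 0.217: SE = √(0.2824 × 6.63/405) = 0.068; power = 0.31. Range 29 to 31%.
- Same between-kebele SD in both arms: 24.5 to 26.2%.

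With k = 0.25 in both arms and unlimited women per kebele, SE = √(0.0625 × 1.3696/15) = 0.0755 and power is still only 26%.

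**Kebeles per arm for 80% power under k = 0.25.** From c = 1 + (1.96+0.84)² × [variance per kebele]/d²:
- Same k: 1 + 7.849 × 0.0961/0.01 = 76.4 (77.2 at m = 24.5).
- Common ICC: 1 + 7.849 × (0.2824 × 6.63/27)/0.01 = 55.4 (56.1 at m = 24.5).

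**Power for 10 points between the extremes** (same formulas, m = 27, normal approximation):

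| k | ICC at 77.6% | Power, same k | Power, common ICC |
|---|---|---|---|
| 0.05 | 0.009 | 91% | 93% |
| 0.07 | 0.017 | 84% | 88% |
| 0.10 | 0.035 | 70% | 78% |
| 0.15 | 0.078 | 48% | 59% |
| 0.20 | 0.139 | 33% | 42% |
| 0.25 | 0.217 | 24% | 31% |

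At m = 24.5 with the same k in both arms, power reaches 80% only for k up to 0.074 (normal) or 0.068 (t).

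**The case against.** The strongest defence is that the trial was sized on the design effect, not on k. The protocol itself says k has no empirical basis and never uses it, so it may be text left over from another formula. Under the design effect actually applied, power is 81 to 87%. This stands to the following extent: a reader might infer that the trial has only 22 to 31% power, and the documents do not support that. They support it only conditionally on k = 0.25. They equally give no support for 1.5.

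k = 0.25 is also large at these proportions. The between-kebele SD would be 0.25 × 0.776 = 0.19 in control and 0.25 × 0.876 = 0.22 under intervention, so the mean plus two SDs exceeds 100%. It is possible, since k can reach 0.54 at 77.6% and 0.38 at 87.6%, but the lowest power figures rest on an ICC of 0.44 in the intervention arm. The common-ICC figures are the milder reading.

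A reader might also convert the SE of 0.080 into a detectable difference of 2.80 × 0.080 = 22.4 points. That is not valid, because 77.6% + 22.4 = 100%, where kebeles cannot vary. A k of 0.25 cannot exist above a mean of 1/(1+0.0625) = 94.1%. At that ceiling the difference is 16.5 points and power is about 52%, so under constant k no difference is detectable with 80% power. Under a common ICC of 0.217 the detectable difference is about 17 points.

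Two further conditions apply. The 77.6% is described as knowledge of breast self-examination, not uptake, and the size of the conflict depends on it. At m = 27 the two assumptions would agree where p/(1−p) = 0.0192/0.0625, that is at about 23.5%. The calculations also take 15 independently allocated kebeles per arm, whereas Figure 2 and the data quality section can be read as allocation by district. Neither point reconciles the two assumptions at the proportion the protocol states.

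**Conclusion.** The contradiction is certain and follows from the protocol's own figures: k = 0.25 and a design effect of 1.5 cannot both hold at 77.6% with 24.5 to 27 women per kebele. Which of them is nearer the truth cannot be told from the document. The stated 80% is therefore wrong as an unconditional claim. It should be corrected before the trial relies on it, because a moderate departure already matters: at k = 0.10, power is about 70 to 78%. The magnitudes assume 77.6% against 87.6%, kebeles of equal size and independent allocation of 15 kebeles per arm.

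**What to change.** Keep one between-kebele assumption in section 3.5.1, justify it, delete the other, and carry it through the calculation. If k is kept, use c = 1 + (z_α/2 + z_β)²[V/m + k²S]/d². If an ICC is kept, derive the design effect from it and from the planned women per kebele.

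With 30 kebeles fixed, replace the unconditional 80% by power for a 10-point difference over k = 0.05 to 0.25, or the matching ICCs. Quote a detectable difference only where it stays below the ceiling.

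Estimate the ICC from the baseline survey of the same kebeles, which the protocol places before allocation, and restate the power. Give the estimate with its uncertainty, and note that k changes with prevalence, so a baseline value does not by itself fix the value at follow-up.

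The cost is a change of protocol wording and one calculation on data already planned. The stated power becomes conditional and probably less favourable. No added kebeles are needed.
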